###### Conceptualization of the move-play-explore nexus and the pedagogical principles

The research team collaboratively conceptualized the move-play-explore nexus using the transformational knowledge gained through both deductive and inductive research studies. This effort shaped the pedagogical principles underpinning the move-play-explore pedagogy and will culminate in a conceptual paper that examines the theoretical positioning of the nexus and proposes shared definitions for movement, play, and exploration. We will first establish a theoretical framework for the move-play-explore nexus within the context of ECE pedagogy, public health, and movement sciences, highlighting the importance of transdisciplinarity in bridging these disciplines to foster holistic child development. We will then develop unified definitions for movement, play, and exploration derived from our literature review and empirical findings. The goal is to ensure that these definitions are applicable across different disciplinary perspectives and practical settings in Norwegian kindergartens. By doing so, the project aims to create a shared vocabulary and conceptual understanding that can be used by kindergarten staff and researchers alike in the MoveEarly project.

##### Sample/material

The material included in the scoping review will result from the literature search. The guided tours with post-tour focus groups will be conducted in 3 kindergartens, including 1–2 staff members together with minimum 3 children in 2 different departments (one with younger children and one with older children), summing to 6 guided tours in total. Staff spontaneous filming will be conducted in the same kindergartens.

##### Analysis plan

The scoping literature review approach will be guided by Arksey & O’Malley [111], Pollock et al. [112] and Westphaln et al. [113]. The review will be reported following the Preferred Reporting Items for Systematic reviews and Meta-Analysis extension for Scoping Review (PRISMA-ScR) guidelines [114]. Briefly, we will follow these stages: 1) Specifying the research question, 2) Identifying relevant literature, 3) Selecting studies, 4) Extracting, mapping and charting the data, 5) Summarising, synthesising and reporting the results, 6) Integrating expert consultation through each of the stages. We will use basic qualitative content analysis to identify key characteristics and/or factors related to the concepts movement, play and exploration [115]. Such an analysis is relevant for scoping reviews and in line with MoveEarly´s objective of informing the development of conceptual framework or theory [112].

The data generated from the guided tours and focus groups will be analysed similar to other qualitative data, as described in the process evaluation (see Sect. "Analysis plan" for details). Briefly, the analysis will be inspired by reflexive thematic analysis (RTA) [116] supported by NVivo (QSR Version 12.6) as a data management tool. The purpose of the analysis will be to develop a systematic overview of *themes*—“defined by meaning-unity and conceptual coherence” [116] (p. 77). In this analysis the themes will provide a systematic overview of children and staff’s situated understandings of movement, play and exploration in kindergartens. This analysis will be supplemented by microanalysis [117] to gain a deeper understanding of the move-play-explore nexus and how to develop a child responsive pedagogy facilitating for movement, play and exploration.

#### Co-creation of a continuing professional development program and intervention delivery

##### Background

The objective of the professional development is to enable kindergarten staff to deliver the components of the intervention at the child level (i.e., the move-play-explore nexus). Thus, through theoretical and practical lectures and workshops and sustained support, the professional development aims to increase staff and kindergarten’s competence and motivation to implement the move-play-explore pedagogy. To achieve this, we co-created the professional development with kindergarten staff and other involved stakeholders [70, 71]. The co-creation process followed the working principles suggested by Smith et al. [70] and was placed within an Integrated Knowledge Translation typology, understood as a collaborative process where researchers work with knowledge users (i.e., kindergarten staff) with the aim of increasing the usefulness and impact of the partnership and research. Intervention development was informed by existing research and our research group’s extensive experiences with intervention and education programming. Evidence on implementation strategies of PA interventions is inconsistent and weak [24, 118]. Of particular importance, the development of the MoveEarly intervention was informed by the experiences and process evaluation of *Active Learning Norwegian Preschool(er)s (ACTNOW)* [27], a large-scale cluster RCT where we promoted a multimodal PA intervention for young children through an intensive professional development for kindergarten staff. In ACTNOW, 77 ECE teachers and directors across 23 intervention kindergartens were provided a 7-month professional development delivered face-to-face, supported by online webinars, an online resource, and portable movement and learning equipment. In our experience, a main challenge is to reach *all* staff with ongoing input and support. This calls for a better mix of face-to-face interaction and digital resources to support staff in understanding, implementing, and sustaining the program in their setting. A stronger focus on online resources may provide enhanced reach as it demands fewer resources for follow-up and can be more flexibly tailored to each centre’s context and schedule. Thus, we expand our existing online resource (https://activeinpreschool.com/) by adding an e-learning toolbox to support the professional development program in MoveEarly. Though a 100% web-based delivery could provide superior reach, our experience is that staff find face-to-face delivery of utmost importance. Thus, we decided on optimal solutions of the professional development and resources together with the kindergarten staff and stakeholders.

##### Design and methods

To anchor the project with each kindergarten owner and seek to develop optimal solutions for all, we conducted a co-creation process organized as 3 separate workshops with each of the 3 owners (i.e., the 2 owners involved in the trial and 1 involved in the feasibility study) January-March 2023 (9 workshops in total). Involving the 3 owners and staff with diverse roles and responsibilities (1 director, 1 teacher and 1 assistant from each kindergarten) made it possible to triangulate input from the different groups and from staff with different positions and needs. The main questions that were discussed during these workshops were: 1) How can kindergartens and researchers together develop pedagogical practices promoting movement, play and exploration? and 2) How can researchers support kindergartens in their development work with movement, play and exploration through professional development, digital resources etc.?

The workshops targeted and discussed 3 areas:First workshops: Staff needs, wants and expectations. We started with presenting the MoveEarly project, including overall aims and activities of the project. We focused on the aim of the professional development, to upskill staff to better promote movement, play and exploration in their kindergarten on an everyday basis, and the processes and resources needed to support them. Together with the staff, we explored success criteria of the project. The professional development and the resources developed in the ACTNOW project along with our experiences and evaluation was used as a point of departure [119]. However, we facilitated a divergent process on what form the MoveEarly professional development and resources could have, in terms of how it could optimally integrate with kindergartens daily operation and foreseeable organization of their development work. We focused on the staff’s opinion on the value and role of (but not limited to)aface-to-face seminars across kindergartens (kindergarten staff visiting the university)bface-to-face seminars in kindergartens (researchers visiting kindergartens)ccollaborative efforts among kindergartens (ways of sharing ideas and experiences)dwebinars and digital resources (lectures, workshops, toolbox)ekindergartens’ written plans (organizational and individual aims and project plans)Second workshop: Program feasibility. Based on the input from kindergarten staff in the first workshop, we developed a draft of the MoveEarly professional development and digital resources. The draft was presented to the staff, with the rationale of this model being to verify our understanding of their needs and wants discussed during the first meeting. We discussed pros and cons of the model to facilitate a convergent process towards developing a possible intervention model, including triangulation of perspectives across owners. We focused on how feasible the proposed model was both for kindergartens and researchers. Our understanding of sustainability as an optimal balance of potential effects and spent resources guided this discussion.

Third workshop: Adaptation. Based on the input from kindergarten staff in the second workshop, we refined and presented the final draft of the MoveEarly professional development program and online resources. The focus of the workshop was to discuss how kindergartens could organize their development work integrating with this model; How could kindergartens adapt to this model, or if challenging, how could the model be fine-tuned? Finally, we asked staff to provide input on content and curriculum of the professional development. However, this part has a minor focus because we addressed staff understanding of the move-play-explore nexus and thus competence needs in the conceptual work (see Sect. " Conceptual groundwork for design of the move-play-explore pedagogy (child level)" for details) and because the curriculum would be evaluated and adapted from the pilot study.

The professional development model developed through these seminars was presented to the user advisory board including various stakeholders, who had the opportunity to provide input based on their diverse roles and viewpoints. The final professional development and online resources were shared with staff taking part in the co-creation and kindergarten owners before we started a feasibility study.

##### Sample/material

The sample involved in the co-creation was staff from 7 kindergartens from each of 3 owners, including a total of 63 staff members. Kindergartens was recruited based on diversity in their size and organization.

To describe and evaluate the co-creation process, a minimum of one researcher observed each of the nine workshops and made notes on the topics discussed, the input received from staff, and the process in general. These data were supported by notes created by the staff during the workshops, for example, post-it notes, posters or similar input. Finally, each participant was asked to complete a brief electronic, anonymous survey at the end of the third workshop to provide feedback on how they experienced the co-creation process and what they found valuable and useful.

##### Analysis plan

Quantitative data from questionnaires will be analysed statistically and results described using relevant measures for different types of data. Procedures for analysis of qualitative data will be similar to procedures described for such data in the process evaluation (see 4.3.2 for details). Briefly, the analysis will be inspired by RTA [116] supported by NVivo (QSR Version 12.6) as a data management tool. The purpose of the analysis will be to develop a systematic overview of *themes*—“defined by meaning-unity and conceptual coherence” [116] (p. 77). In this analysis the themes will provide a systematic overview over the themes capturing participants’ perceptions and contributions to the main aspects discussed during co-creation workshops. This means that the initial codes will be anchored in the co-creation main objectives (such as: staff’s needs and expectations, program feasibility and adaptation), while the constructed themes will closely follow the terms and meaning patterns occurring in the empirical material.

A more detailed account of the co-creation process and results will be published in a separate paper.

##### Feasibility study

The professional development developed through the co-creation process (described in Sect. " Intervention and theoretical framework") was piloted with 7 kindergartens over a 7-month period from November 2023 to May 2024. All kindergartens received the intervention, that is, there were no between-group comparisons nor any outcome evaluation of this study. Researchers’ experiences with provision of the professional development and the implementation process in kindergartens along with feedback from staff through focus groups and an evaluation questionnaire was used to fine-tune the intervention before starting the main trial. Main feedback was that kindergartens implemented the intervention well and that staff found participation in the project valuable and were satisfied with the collaboration with researchers. Given the positive feedback from staff, which was largely consistent with our experiences, we did only minor adjustments to the intervention:

Written work. We provided a stricter template for the project plan. Originally, this task was less concrete to allow for flexibility in structuring and content. However, we learned that this plan needed more structure to ease the writing, to connect more strongly with the pedagogical principles, to target concrete action points and provide milestones of the implementation process to move the project forward with regard to timelines, responsibilities, meeting points etc. This change structured the writing of the plan, but did not limit kindergartens’ flexibility in implementing the intervention.Integration of intervention components: We learned that we should put more emphasis on integrating the different intervention components to help kindergartens staff see how they connect. This meant a better integration of online resources and the ideas bank in physical seminars to provide concrete, hands-on experiences with the resource and activities. Thus, during seminars, we provided more information on the online resource (i.e., its intention, content and structure), staff was provided more time to explore it on their own and discuss it with peers, and we included multiple activities in practical sessions so staff could learn how activities worked and how they could be structured and adapted.

### Outcome evaluation

#### Measurements

MoveEarly will include comprehensive measures of child-level effects to capture whole-child development. We will not collect data on adverse events or unintended effects since we do not foresee increased risk of the intervention beyond normal practice. Each data collection will be conducted over a 2-month period and will be organised in close collaboration with kindergartens. All measurements will be performed in the field (i.e., kindergartens) to provide a safe environment for children and avoid travel and disturbance to kindergartens’ practices. Missing data will be minimized by scheduling extra visits to centres if children are not available due to sickness etc.

##### Movement competence and creativity

Movement competence and creativity will be measured using the “River Challenge”, which is being developed for this project. A brief description of its rationale, development and evaluation is provided in Sect. "Analysis plan".

In the River Challenge, children will be invited to take part in three challenges. The first challenge (“Crossing the river”) is based on locomotor and balance skills and the second challenge (“Rescuing the elephants”) on object control skills. In addition, each challenge will capture children’s creativity in and through movements, with a final challenge (“Creating an animal playground”) based on free play to capture creative thinking. The focus of the instruments is on adaptation of these skills to successfully achieve the challenges, rather than measurement of specific skills. Each challenge is presented as a story based on rescuing a variety of animals. This idea is based on Conceptual Playworlds [99], which is a method encouraging children to interact with stories that are personally meaningful to them, rather than responding to adults’ direct instructions. This method encourages adaptability and creativity as there are no specific methods/skills required to be used.

The challenges will be set up within the children’s daily kindergarten setting. The maximum space required will be 2 × 3 m to make it feasible for field testing. The children will be tested one-by-one to capture their own personal skilfulness, adaptability and creativity, rather than being influenced to provide solutions by others. Thus, tests will be conducted in a separate room or space. Tasks will be completed in a standardised order, using approximately 20 min per child. The test teams will consist of one instructor who tells the story, while a separate assessor observes and scores the child’s performance. Both challenges have eight levels (i.e., items), which will be scored based on successful or unsuccessful achievement. There will be no specific method/skills required to achieve each challenge, however detailed and standardized descriptions of what is ‘successful’ and ‘unsuccessful’ will be a fundamental aspect of the scorers' training. Scores are summed for each item and challenge.

Challenge one will be set up as a river crossing where children are invited to cross from one riverbank (a set of folded mats) to another, using stepping stones to rescue a variety of objects. The story suggests that some frogs have gone on an adventure across the river and need to be rescued. The children then use the stepping stones to cross the river, without falling in, pick up the differing sizes of objects and bring them back across. At each level, the number or stability of the stepping stones is reduced and/or the objects are changed (from picking up 2 small bean bags to a yoga ball and a heavy medicine ball). Children need to demonstrate a variety of different locomotor and balance skills and adaptable solutions to successfully manage the challenge as the environment changes.

Challenge two will be set up as a situation where children are invited to retrieve and throw different sized balls at different sized objects and to use different equipment to retrieve moving objects. The story used to engage children is one of various elephants (represented by various sizes of yoga balls) have become stuck in the mud and need help to get out. The suggestion is to throw a variety of sizes of balls to the target to move the yoga ball. The size of each ball to be caught and thrown and the size of the target is reduced to increase difficulty as each level progresses. In the conclusion of this challenge the children are asked if they want to catch some fish swimming down the river. These are small balls rolled down a ramp, to standardize the speed, and the children try to scoop the balls up in a short fishing net first, followed by a longer fishing net, from the riverbank. Children need to demonstrate a variety of different object control skills to successfully manage the challenge as the environment changes.

Movement creativity challenges are also included where children are encouraged (through the story) to find different solutions to movement challenges. The creative thinking challenge involve free use of a set of predefined resources (mats, hoops, sticks, cones, ropes, paper cups, blankets and cloths pegs). This challenge will not include any instructions besides an idea to inspire creativity. The child will have up to 5 min to create a play environment/playground for the animals introduced in the first challenges. Creativity will be scored based on fluency and originality. Fluency refers to the number of different solutions the child finds to achieve the task. Originality refers to the type of solution the child demonstrates on a scale from no response to predictable, less predictable, new, unique or original response. These categories will be determined using the data from the baseline testing. The lower the frequency of a response, the higher the originality score will be [120].

More details about the test, scoring procedures and measurement properties will be published in a separate paper.

##### Physical activity, sedentary time and screen time

We will assess PA using the ActiGraph GT3X + accelerometer [121], which is the most used and validated accelerometer in the field [122, 123]. We will instruct children to wear the accelerometer on the right hip 24 h per day for seven consecutive days, except during water activities like swimming and showering. Accelerometers will be initialized using a sampling rate of 30 Hz. Files will be analysed using a custom-made script in MATLAB applying 1 s epochs to correctly capture the lower and higher intensity levels [124, 125]. Consecutive periods of ≥ 20 min of zero counts will be removed as non-wear time [126, 127]. We will report results for overall PA level (counts per minute (cpm)) and apply the previously established and validated Evenson et al. cut points [128, 129] to determine minutes per day spent sedentary (SED) (< 100 cpm), in light PA (LPA) (100–2295 cpm), in moderate PA (MPA) (2296–4011 cpm), in vigorous PA (VPA) (≥ 4012 cpm), and in moderate-to-vigorous PA (MVPA) (≥ 2296 cpm). As appropriate, sensitivity analyses will be conducted using the Pate et al. cut points [130].

Adding to the traditional PA intensity profile, we will include a higher resolution PA descriptor of time per day spent in 17 narrow intensity intervals across the intensity spectrum; 0–99, 100–999, 1000–1999, …, 14,000–14,999, and ≥ 15,000 cpm. Similar to previous applications [131–134], this dataset will be used to investigate more nuanced PA signatures associated with relevant outcomes.

To assess intervention effects on overall PA levels, as well as in care and out of care to assess possible compensatory behaviour outside the kindergarten domain [20, 135], we will assess PA levels over the full week, weekdays and weekend days separately, as well as PA for the whole day (06:00–21:59) and for care hours (08:30–15:30) and afternoon hours (15:30–21:59) on weekdays. Wear-time requirements will be ≥ 8 h/day and ≥ 3 weekdays + ≥ 1 weekend day for whole days and ≥ 5 and ≥ 3 h/day of monitoring for ≥ 3 weekdays for care hours and afternoons, respectively.

We will assess screen time using a parent questionnaire adapted from the Sunrise study [136].

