##### Sleep

We will assess children’s sleep using 24-h accelerometry and a parent questionnaire. From accelerometry, we will estimate sleep using an algorithm developed and validated to identify sleep/bedrest from waist-worn triaxial accelerometers in 3–6-year-old children [144]. First, the *PhysicalActivity* (v0.2.4) R package is used to remove non-wear periods, defined as ≥ 90 min of consecutive zero counts allowing 2 min of interruptions. Second, the *PhysActBedRest* (v1.1) R package is used to determine sleep using vector magnitude data at 60 s epochs [144]. This algorithm has good sensitivity (0.94), specificity (0.97), and accuracy (0.95) as compared with visual identification of accelerometry-measured sleep periods. In the questionnaire, used in the Sunrise study [136], parents report children’s sleep duration including nap time, when they go to bed and when they wake up, and the consistency of these patterns. Children’s sleep quality is rated on a 1–7 scale.

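### Sedentary time, counts per minute and the 0–99 cpm interval take in an uncontrolled share of sleep in the whole-day and afternoon windows, because the stated processing has no sleep exclusion

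*Protocol article*

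**What the plan says.** All references are to the Protocol article, Outcome evaluation, Measurements.

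The section on physical activity, sedentary time and screen time tells children to wear the device "24 h per day for seven consecutive days, except during water activities like swimming and showering". Files are processed in 1 s "epochs to correctly capture the lower and higher intensity levels". Sedentary time is everything below 100 cpm, with no condition that the child be awake. The finer descriptor has 17 intervals, the lowest being 0–99 cpm. Results are given for the full week, weekdays and weekend days, "as well as PA for the whole day (06:00–21:59) and for care hours (08:30–15:30) and afternoon hours (15:30–21:59) on weekdays". The one exclusion named is for zero-count runs of at least 20 minutes: "min of zero counts will be removed as non-wear time". A whole day needs at least 8 h of wear, and a weekday afternoon at least 3 h.

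The Sleep section uses 24 h accelerometry for another purpose: "we will estimate sleep using an algorithm developed and validated to identify sleep/bedrest from waist-worn triaxial accelerometers". That processing works on 60 s vector-magnitude data. Its non-wear rule is at least 90 minutes of zeros with 2-minute interruptions allowed. It reports a sensitivity of 0.94 and a specificity of 0.97 against visual identification. Nothing connects its sleep periods to the activity windows.

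**The concern.** Participants are aged 4 to 6 over the study (Table 1), so windows that open at 06:00 and close at 21:59 can be expected to contain sleep. The 20-minute zero rule is the only thing standing between that sleep and the activity variables, and it sorts sleep by stillness. A motionless stretch is deleted as if the device were off. A stretch broken by movement stays in as sedentary wear time. A child's sedentary total, cpm and valid wear time then depend partly on when and how restlessly the child sleeps.

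Two uses are most exposed:

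- **The afternoon window.** It serves the stated check for compensation outside kindergarten, and a larger share of it is sleep than of the whole day.
- **The association analyses.** These are cross-sectional and longitudinal and may use sedentary time, cpm or the 0–99 cpm interval. Randomisation gives them no protection if sleep is itself related to the child outcomes.

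**Working it through.** The article gives no figure to reproduce here, so this is window arithmetic on its stated rules plus labelled assumptions.

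**Inputs from the article.** Whole-day window 16 h = 960 min; afternoon window 6.5 h = 390 min; exclusion of zero runs of at least 20 min; 1 s epochs; wear minima of 8 h = 480 min and 3 h = 180 min.

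**Assumptions, not in the article.** Sleep onset 19:00–21:00; waking 06:30–07:30; retained share *f* of sleep, meaning the part that the 20-minute rule does not remove, anywhere from 0 to 1; retained sleep contributes about zero counts.

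**Step 1, what the zero rule does.** Twenty minutes is 20 × 60 = 1,200 consecutive 1 s epochs. No interruption allowance is stated. If the rule runs on the 1 s data, one non-zero second breaks the run, so *f* depends on movement during sleep. A still half-hour at 21:00 is non-wear under this rule, but it survives the 90-minute rule in the Sleep section and can be classed there as sleep.

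**Step 2, sleep inside the windows.** Whole day: (22:00 − onset) + (waking − 06:00). Afternoon: 22:00 − onset.

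**Step 3, effect.** Added sedentary minutes = *f* × sleep in window. The cpm factor is awake ÷ (awake + retained).

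| Onset / waking | Sleep, day | Sleep, afternoon | Added sedentary min at *f* = 0.5 (day / afternoon) | cpm factor at *f* = 0.5 | cpm factor at *f* = 1 |
|---|---|---|---|---|---|
| 21:00 / 06:30 | 60 + 30 = 90 | 60 | 45 / 30 | 870/915 = 0.95; 330/360 = 0.92 | 0.91; 0.85 |
| 20:00 / 07:00 | 120 + 60 = 180 | 120 | 90 / 60 | 780/870 = 0.90; 270/330 = 0.82 | 0.81; 0.69 |
| 19:00 / 07:30 | 180 + 90 = 270 | 180 | 135 / 90 | 690/825 = 0.84; 210/300 = 0.70 | 0.72; 0.54 |

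At *f* = 0 nothing is added and both factors are 1. Sleep makes up 90/960 to 270/960 (9% to 28%) of the whole-day window and 60/390 to 180/390 (15% to 46%) of the afternoon window.

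**Step 4, wear minima.** In the middle row with *f* = 0.5, a day qualifies with 480 − 90 = 390 min of waking wear and an afternoon with 180 − 60 = 120 min. At the extreme (onset 19:00, *f* = 1), 180 min of retained sleep meets the afternoon minimum unaided.

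**Step 5, between arms.** If sleep onset were 10 min earlier in one arm and half of that time were retained, the error in that arm's sedentary time relative to waking sedentary time would rise by 10 × 0.5 = 5 min. The article gives no SD for sedentary time, so this cannot be put on its effect-size scale.

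**The case against.** The strongest reply is that the article is silent on sleep rather than stating that it is kept. Files pass through a custom script, and the data management section refers to a protocol manual that is not shown, so a mask may already exist. That possibility stands. But the section is no loose summary: it fixes the epoch, the non-wear rule, the cut points, the clock hours and the wear minima. Anyone following it as written would leave sleep with movement in.

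The second reply is that the size may be small. This also stands. The windows already leave out the eight hours from 22:00 to 06:00, the zero rule removes still sleep, and sleep times and retained share are assumptions.

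A reader might infer three stronger things that the article does not support:

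- **That the intervention effect on activity is biased.** This needs sleep timing or restlessness to differ by arm, and nothing in the article predicts that. Otherwise the error is common to both randomised arms, and the model adjusts for the baseline level of the outcome.
- **That all the activity outcomes are compromised.** Light, moderate, vigorous and moderate-to-vigorous minutes are little affected, care hours only through naps, and compensation can still be read from afternoon light and moderate-to-vigorous minutes. Movement competence and creativity, the priority outcomes, do not come from the accelerometer.
- **That all sleep in the windows is scored as sedentary.** The zero rule removes an unknown part of it.

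The last reply is that masking has its own error, because the algorithm detects bedrest as well as sleep. With a specificity of 0.97 spread evenly over the 690–870 waking minutes above, 0.03 × 690 to 0.03 × 870, or about 21 to 26 min a day, would be masked wrongly. This is a real downside, and it is a reason to report both versions rather than to leave the windows unmasked.

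**Conclusion.** The point holds for sedentary time, cpm, the 0–99 cpm interval and valid wear time in the 06:00–21:59 and 15:30–21:59 windows. Under the assumed sleep times, 90–270 min of the whole-day window and 60–180 min of the afternoon window are sleep. The amount retained can be anywhere from none of it to all of it, and the article does not fix where a child falls. In the randomised comparison the main consequence is noise and dilution, with bias only if sleep differs by arm. The afternoon compensation analysis, and the association analyses that use these three measures, are the most exposed. The point is worth settling because the article already derives the sleep periods needed to deal with it.

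**What to change.** Before computing sedentary time, cpm, the 0–99 cpm interval and valid wear time for the whole-day and afternoon windows, mask the sleep/bedrest periods from the algorithm in the Sleep section. Define these outcomes as waking wear within the window. Apply the mask identically in both arms and blind to allocation, settle it before the database lock described under data management, and report the unmasked version as a sensitivity analysis. If the processing script already does this, one sentence in the activity section is enough.

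The cost is processing work, with no new data:

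- The 60 s sleep output has to be aligned with the 1 s activity data.
- The 20-minute and 90-minute non-wear rules have to be reconciled, including which applies first.
- Some quiet waking time in bed will be masked.
- Some days will have fewer valid hours and may fall below the wear minima.
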